## Abstract

**Background:**

Metabolic syndrome is recognized as one of the most common global health issues, which may cause numerous side effects. Studies have shown the favorable effects of probiotic supplements on glycemic indices, lipid profiles, and oxidative stress status. However, the number of studies investigating the effects of food products containing probiotics and prebiotics on metabolic diseases is limited. Limited evidence also shows that products containing Lactobacillus plantarum could affect metabolic alterations in chronic diseases. No previous study evaluated the impact of synbiotic yogurt containing Lactobacillus plantarum on people with metabolic syndrome. Therefore, the current study aims to investigate the effect of the newly developed synbiotic yogurt containing Lactobacillus plantarum, Lactobacillus pentosus, and Chloromyces marcosianos yeast on the components of metabolic syndrome, oxidative stress status, and some other risk factors for cardiovascular diseases in adults with metabolic syndrome.

**Methods:**

In this study, 44 patients with metabolic syndrome will be randomly assigned to intervention and control groups in a randomized, double-blind, controlled clinical trial. Participants in the intervention group will consume 300 g of synbiotic yogurt daily, while those in the control group will consume 300 g of regular yogurt daily for 12 weeks. Anthropometric measurements, blood pressure, and biochemical parameters will be evaluated before and after the intervention.

**Discussion:**

The management of the metabolic syndrome presents significant clinical challenges. While probiotic supplementation for these individuals has been considered, the consumption of probiotic-rich foods has received considerably less attention.

**Trial registration number:**

Iranian Registry of Clinical Trials (IRCT20220426054667N1) (2022–05-18).

## Introduction

The Metabolic syndrome (MetS) is recognized as one of the most common global health issues [1]. Lifestyle modifications, such as improving eating habits and physical activity, are the main therapeutic strategies to manage MetS complications [2]. Numerous side effects, such as type 2 diabetes, cardiovascular disease, non-alcoholic fatty liver disease, polycystic ovary syndrome, several types of cancer, inflammatory bowel disease, and chronic kidney disease, are common in subjects with MetS [3]. Insulin resistance, hypertension, dyslipidemia, and visceral obesity are the components of MetS according to the National Cholesterol Education Program (NCEP) criteria [4].

Studies have shown that oxidative stress, inflammation, and insulin resistance are considered major factors in the pathophysiology of the MetS [5]. By inducing lipolysis in adipose tissue, insulin resistance causes a high quantity of free fatty acids to be released into the bloodstream, which increases the oxidation of free fatty acids and the generation of reactive oxygen species (ROS) [6]. The increase in ROS production leads to oxidative stress and a decrease in antioxidant defenses [7]. Oxidative stress results in the conversion of low-density lipoprotein (LDL) to oxidized low-density lipoprotein (ox-LDL), which has been shown to be increased in patients with MetS [8]. Ox-LDL exerts cytotoxic effects on vascular endothelial cells and is a significant contributor to atherosclerosis and endothelial dysfunction [9]. In addition, it causes the endothelial barrier to break down and reduces the bioavailability of nitric oxide (NO) [10]. In addition, individuals with MetS have been shown to have higher levels of malondialdehyde (MDA), a marker of lipid peroxidation in oxidative stress conditions [11]. Understanding the pathogenic processes that contribute to the development and progression of MetS, as well as modifying associated risk factors, are crucial to the management and treatment of the disease [12].

In recent years, the importance of the gut microbiome in the pathogenesis of metabolic disorders associated with MetS has been highlighted [13]. Dysbiosis or imbalance in the gut microbiome may contribute to the development of oxidative stress, inflammation, and other cardiometabolic risk factors [14]. The composition of the gut microbiome can be modified by a variety of methods. Consuming probiotics and prebiotics is one of these methods [15]. It has been shown that probiotics and synbiotics play a crucial role in controlling MetS risk factors such as dyslipidemia, insulin resistance, abdominal obesity, blood pressure, and atherosclerosis [16]. In addition, probiotics help to reduce oxidative stress by regulating ROS-producing enzymes, enhancing the activity of antioxidant enzymes, and eliminating oxidant compounds from the gut or preventing their production [17]. Furthermore, active peptides are produced by probiotic bacteria and can function as antioxidants [18].

The newly developed synbiotic yogurt that will be used in this study contains native strains of Lactobacillus plantarum, Lactobacillus pentosus, and Chloromyces marcosianos yeast [19]. In human studies, probiotic supplements containing Lactobacillus plantarum have been demonstrated to improve glycemic indices, lipid profiles, and oxidative stress [20]. Besides, limited evidence shows that products containing Lactobacillus plantarum could favorably affect metabolic and oxidative alterations in chronic diseases [21]. However, the number of studies investigating the effects of probiotic and prebiotic food products on metabolic diseases is limited. On the other hand, no studies have been conducted to evaluate the effect of synbiotic yogurt consumption containing Lactobacillus plantarum in people with MetS. In order to develop effective approaches for the prevention and management of the MetS complications, the current study aims to investigate the effect of the newly developed synbiotic yogurt containing Lactobacillus plantarum, Lactobacillus pentosus, and Chloromyces marcosianus on the components of MetS, oxidative stress status, and some other risk factors for cardiovascular diseases in adults with MetS.

## Material and methods

The study protocol has been approved by the ethics committee of Tehran University of Medical Sciences (ethics number: IR.TUMS.MEDICINE.REC.1401.080). Participants will be given a comprehensive explanation of the study's objectives, methods, benefits, and risks. All participants will also be informed that taking part in the research is completely voluntary, and they can quit at any time that they want. A written informed consent will be collected from every participant prior to the study's enrollment. The trial was registered at the Iranian Registry of Clinical Trials (www.irct.ir) with the number IRCT20220426054667N1.

### Participants

This study will be conducted as a parallel randomized clinical trial with an allocation ratio of 1:1. Patients with MetS aged 30 to 50 and body mass index (BMI) of 25 –35 kg/m^2^ will be recruited from health centers affiliated with Yasouj University of Medical Sciences, Yasouj, Iran. MetS will be confirmed based on the ATP III criteria when at least three of the following criteria are met: waist circumference (WC) > 102 cm in men and > 88 cm in women, triglyceride (TG) ≥ 150 mg/dl, high-density lipoprotein (HDL) ≤ 40 mg/dl in men and ≤ 50 mg/dl in women, blood pressure ≥ 130 to 85 mmHg, and fasting blood sugar (FBS) ≥ 100 mg/dl.

We will exclude those followed weight loss programs or weight changes of more than 10% of initial weight during the last six months; professional athletes or subjects with any changes in the intensity and quantity of physical activity in the previous four weeks; pregnant, lactating and postmenopausal women; those who have allergy to dairy products and probiotics; smokers and alcoholic beverage consumers; those who routinely consume probiotic or synbiotic yogurts; individuals with cardiovascular, lung, nervous system, kidney, liver, thyroid, and other endocrine diseases, diabetes, cancer, and eating disorders; taking drugs that affect appetite, body weight, and lipid metabolism, corticosteroids, oral contraceptives, antidepressants and antipsychotics, lipid lowering medications, antibiotics, antidiabetic and blood pressure medications (uncontrolled blood sugar and blood pressure); receiving probiotics and other dietary supplements in the last three months.

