### Study design

Prior to the primary intervention, all selected individuals will participate in a two-week "run-in" period during which relevant questionnaires are used to gather information regarding sociodemographic variables, the history of diseases, drug and supplement use, dietary intakes, and physical activity levels. At the end of the run-in period and before the start of the intervention, people will be randomly assigned to the intervention and control groups. A computerized randomization will be carried out using a block randomization procedure of size 2 and 4, stratified by gender (male or female), and BMI (25–30 or 30–35 kg/m^2^). Each patient will get an identity number, which will be input into the computer's randomization program together with the codes of patients who have the same age and BMI. The intervention or control groups will ultimately be randomly allocated to patients with the same conditions. Random allocation will be performed by a person unaffiliated with the study. Subjects in the intervention group will consume 300 g of synbiotic yogurt and those in the control group will consume 300 g of regular yogurt daily for 12 weeks (Fig. 1). Participants will be asked not to change their regular physical activity and usual dietary intakes during the study. They will also be asked not to use any other probiotic or synbiotic products while participating in the trial. The participants' dietary intake will be evaluated again at the end of the sixth week as well as at the end of the trial in order to evaluate the patients' nutritional intake during the study and to ensure yogurt consumption. Physical activity level will also be assessed during the sixth week and the last week. Blood samples (10 cc) will be obtained after a 12-h overnight fast at baseline and at week 12 for biochemical measurements (Table 1).

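### As worded, the three-month look-back covers probiotics and supplements but not antibiotics, so a patient who recently finished a course appears eligible

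*Protocol article*

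**What the plan says.** The exclusions in the Participants section form one long sentence divided by semicolons. Three items carry their own look-back:

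- weight: "weight changes of more than 10% of initial weight during the last six months"
- physical activity: "any changes in the intensity and quantity of physical activity in the previous four weeks"
- probiotics and supplements: "receiving probiotics and other dietary supplements in the last three months"

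The drug item comes just before the last of these. It opens "taking drugs that affect appetite, body weight, and lipid metabolism, corticosteroids, oral contraceptives, antidepressants and antipsychotics" and ends, with the start of the next item, "lipid lowering medications, antibiotics, antidiabetic and blood pressure medications (uncontrolled blood sugar and blood pressure); receiving probiotics". No period is attached to it.

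Study design describes a two-week run-in in which questionnaires record, among other things, drug and supplement use. It sets no rule about antibiotics. The restriction during the trial names only other probiotic and synbiotic products.

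On rationale, the Introduction states: "Dysbiosis or imbalance in the gut microbiome may contribute to the development of oxidative stress, inflammation, and other cardiometabolic risk factors". The Discussion adds that probiotics can change the gut bacteria and so lower risk factors for metabolic syndrome.

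**The concern.** The protocol treats antibiotics as relevant enough to exclude current users, and earlier probiotic or supplement use as relevant for three months. It gives no reason for a shorter reach in the case of antibiotics. If the gut bacteria are part of the route by which the yogurt works, a recently completed course bears on that route at least as plausibly as a supplement taken weeks earlier.

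Three things are at stake. Recent users may show outcome changes over the 12 weeks that have nothing to do with the allocated yogurt, which adds variance. They may respond differently to the yogurt, which blurs the estimated effect. With 22 patients per arm they may also fall unevenly between arms. In addition, recruiters may apply the criterion differently, some literally and some assuming that the closing time window covers the drug list.

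**Working it through.** The plan states no figure on this point, so there is none to reproduce. The first two steps are textual. The rest are illustrations on labelled assumptions.

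**1. Which window governs which item (Participants).**

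| Item | Verb or form | Look-back |
|---|---|---|
| Weight change | past event | six months |
| Change in physical activity | past event | four weeks |
| Drugs, including antibiotics | taking | none |
| Probiotics and other supplements | receiving | three months |

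Each stated window sits inside its own item. A semicolon and a new verb separate the antibiotic item from the three-month window. Nothing in Study design, the visit table or the intervention section supplies an antibiotic window.

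**2. The shortest gap the text allows.** The visit table puts the run-in visit at day −14, and first yogurt and baseline blood at day 0. If eligibility is settled at the start of the run-in, a course ended the day before it leaves 14 + 1 = 15 days to baseline. The window for probiotics is three months, about 13 weeks.

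**3. How many patients.** Assumption: 10–20% of otherwise eligible adults had a course in the previous three months. Then 0.10 × 44 = 4.4 and 0.20 × 44 = 8.8, or about 4 to 9 patients.

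**4. Chance imbalance.** Take 6 recent users among 44 and treat allocation as a simple 22/22 split. The chance of a 5–1 or 6–0 division is

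2 × [C(22,6) + C(22,5) × C(22,1)] / C(44,6) = 2 × (74,613 + 579,348) / 7,059,052 = 0.185.

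**5. What such a split would do to triglycerides.** Assume an SD of about 20 mg/dl (the Sample size section gives 21.1 and 19.6) and a drift of one full SD in every recent user.

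- 5–1 split: (5 − 1)/22 × 20 = 3.6 mg/dl
- 6–0 split: 6/22 × 20 = 5.5 mg/dl
- Standard error of the difference: 20 × √(2/22) = 6.0 mg/dl

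Even the 6–0 split shifts the difference by less than one standard error.

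**6. Added noise.** If a fraction p of patients drift by k SDs, the variance is multiplied by 1 + p(1 − p)k².

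| p | k | Variance factor | SD factor | Equivalent patients per arm (22 ÷ variance factor) |
|---|---|---|---|---|
| 0.10 | 0.5 | 1.0225 | 1.01 | 21.5 |
| 0.20 | 0.5 | 1.04 | 1.02 | 21.2 |
| 0.10 | 1 | 1.09 | 1.04 | 20.2 |
| 0.20 | 1 | 1.16 | 1.08 | 19.0 |

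The loss is between about half a patient and three patients per arm. Both p and k are assumptions; the article documents neither.

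**The case against.** **The authors may have meant the window to cover the drugs too.** The exclusion sentence is loosely written. Its last two items are parallel participles, so the closing period could have been intended for both. This is also a condensed article, and the full protocol may hold drug-specific windows. That stands as a caution, and it is why the point says *appears eligible*. It does not remove the point: the article does state look-backs, the punctuation ties this one to probiotics and supplements, and a recruiter following the text would admit recent antibiotic users.

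**There is no bias.** This stands. Recent users are balanced between arms in expectation, and the 18.5% chance of a lopsided split would apply to any trait carried by 6 of 44 patients. The standard error already allows for such imbalance, so a reader who took that percentage as a measure of harm would be reading too much into it. Baseline-adjusted ANCOVA helps with differences present at day 0, but not with values still changing afterwards.

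**The run-in gives some distance.** This also stands. A reader might infer that a course could end the day before the first yogurt. That holds only if eligibility is settled at randomization. The article has selected patients enter the run-in first, which gives about 15 days.

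**The microbiome is not the only route.** Correct. The Introduction says only that dysbiosis may contribute, and it also describes effects on oxidant and antioxidant enzymes and active peptides. No microbiome outcome is measured. The inconsistency is therefore with a partial rationale, not a sole mechanism.

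**Lipid-lowering drugs and corticosteroids share the same wording.** A reader might extend the point to them and argue that triglycerides would still be moving after such a drug is stopped. The documents offer nothing on the timing or size of such a drift, and the gut-bacteria rationale does not carry over, so the point is confined to antibiotics.

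**Conclusion.** The inconsistency is real on the text. The three-month window reaches probiotics and supplements, antibiotics are excluded only during use, and no other section closes the gap. This is a cheap improvement to an eligibility criterion, not a threat to the trial's validity.

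The size depends on two quantities the article does not give: how many entrants are recent users, and how far their outcomes drift. Over the assumed ranges the cost is modest, and it could be smaller still if recent users prove rare. Effect modification cannot be sized from the documents.

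The conclusion rests on reading the semicolons as they stand. If the full protocol already applies a window to antibiotics, only the article's wording needs correcting.

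**What to change.** Reconcile the two exclusion items by placing antibiotics under the look-back the protocol already sets, for example: *use of antibiotics, probiotics or other dietary supplements in the last three months*. Check it from the drug and supplement history already taken in the run-in. Leave the rest of the drug item as it is.

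The three months is the protocol's own figure for probiotics and supplements. The documents do not derive a period specific to antibiotics. If the sponsor intends a different window for them, the article should state it and give the reason for the difference.

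The cost is one line of eligibility text and a few more screen failures or deferred entries. No new data are collected, and no patient is asked to change or stop a treatment. The change governs entry only; it does not address antibiotics started during the 12 weeks.

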### Sample size calculation

Sample size was calculated using the following formula, with inputs including the mean and standard deviation of TG changes in the intervention (212.8 ± 21.1) and control (201.9 ± 19.6) groups obtained from the Cicero et al. study [21], 95% confidence, and 80% power of the test. The minimum sample size in each group was calculated to be 17 cases. However, after adjusting for possible dropouts, this number increased to 22 cases in each group.

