### Statistical methods

Data will be analyzed using SPSS software version 23. The normality of the distribution of the variables will be checked by the Kolmogorov–Smirnov test. All normal distributed quantitative data will be reported as mean ± standard deviation, and qualitative data will be reported as frequency (percentage). Analyses of non-normal variables will be performed after logarithmic transformation. Comparisons of baseline characteristics will be performed using independent t-test (for quantitative data) and chi-squared test (for qualitative data). Analysis of covariance (ANCOVA) test will be used to compare the effect of the intervention between the two groups by adjusting baseline values and confounding variables. A paired t-test will be used for within group comparisons. P < 0.05 will be considered to be statistically significant.

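### The stated inputs call for about 55 patients per group, not 17; on those inputs an unadjusted comparison has about 33% power with 17 per group and 41% with 22, not 80%

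*Protocol article*

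**What the plan says.** The section Sample size calculation in the protocol article names its inputs as the "mean and standard deviation of TG changes in the intervention (212.8 ± 21.1) and control (201.9 ± 19.6) groups", taken from an earlier published study, together with "95% confidence, and 80% power of the test". It concludes: "The minimum sample size in each group was calculated to be 17 cases". Allowing for dropouts, at a rate it does not give, it raises this to 22 per group. The abstract carries the total forward: "44 patients with metabolic syndrome will be randomly assigned to intervention and control groups".

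The section Participants describes a "parallel randomized clinical trial with an allocation ratio of 1:1". The section Statistical methods plans an ANCOVA adjusted for baseline values and confounders, and sets the threshold: "P < 0.05 will be considered to be statistically significant". Neither section gives a correlation between baseline and follow-up TG.

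**The concern.** The difference between the printed means is 10.9 and both SDs are near 20, so the standardised effect is a little over one half. Seventeen per group is about what 80% power needs for an effect of one full SD. The paragraph therefore claims a precision that its own figures do not support, and it is the only justification in the article for enrolling 44 people. A reader who takes the 80% at face value will give a non-significant TG result more weight than it can bear.

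The label on the inputs is a second problem. A mean TG change above 200 is hard to credit in a population where one of the five qualifying criteria (any three suffice) is TG of at least 150 mg/dl. The figures look like TG levels. Read as levels, the intervention value is the higher one, which is not the direction of benefit. Read as reductions, the direction is favourable but the size is implausible. The paragraph prints no units and does not say which reading is meant.

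**Working it through.** **Inputs**

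- From Sample size calculation: means 212.8 and 201.9, so Δ = 10.9; SDs 21.1 and 19.6; power 80%; 95% confidence.
- From Participants: parallel groups, 1:1.
- Assumed: a two-sided 5% test, since sidedness is not stated. The one-sided result is shown below.

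**Attempt to reproduce 17 per group**

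For two independent means, n per group = (z₀.₉₇₅ + z₀.₈₀)² × (s₁² + s₂²) / Δ².

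- (1.960 + 0.842)² = 7.849
- 21.1² + 19.6² = 445.21 + 384.16 = 829.37
- 10.9² = 118.81
- n = 7.849 × 829.37 / 118.81 = 54.8, so **55 per group**. The noncentral t distribution gives 56 (power 80.2%; at 55 it is 79.4%).

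Variants that use only the printed inputs also miss 17:

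| Variant | n per group |
|---|---|
| Two-sided, as above | 55 |
| One-sided 5% | 44 |
| Factor of 2 wrongly omitted, two-sided | 28 |
| Factor of 2 wrongly omitted, one-sided | 22 |
| Factor of 2 omitted and one SD only | 20 to 30 |

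To obtain 17, one of the inputs must change:

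- Difference: √(7.849 × 829.37 / 17) = 19.6, instead of 10.9; or
- Common SD: about 11.3, instead of about 20.4; or
- A correlation term that the paragraph does not mention: about 0.70 in a paired-type variance, which does not fit a parallel design, or about 0.83 in an ANCOVA variance (normal approximation).

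**Power on the printed inputs, unadjusted**

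Root-mean-square SD = √(829.37 / 2) = 20.36, so d = 10.9 / 20.36 = 0.535. Two-sided 5% t-test, noncentral t:

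| n per group | Power for 10.9 | Difference detectable with 80% power |
|---|---|---|
| 17 | 32.8% | 20.2 |
| 22 | 41.1% | 17.6 |

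The 22 already contains the dropout allowance, so 41% applies only if nobody is lost.

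**Power with baseline-adjusted ANCOVA**

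If the SDs are for TG levels, adjusting for baseline multiplies the residual SD by √(1 − r²), where r is the baseline-to-week-12 correlation. The protocol gives no r, so the values below are assumptions (noncentral t, one covariate):

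| Assumed r | Power, 17 per group | Power, 22 per group |
|---|---|---|
| 0.5 | 42% | 52% |
| 0.7 | 56% | 68% |
| 0.8 | 71% | 82% |

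Power of 80% needs r of about 0.84 with 17 per group, or about 0.79 with 22. If the SDs really are for changes, as labelled, this calculation does not carry over: a change score already uses the baseline, and the further gain from ANCOVA would be smaller.

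**The case against.** There are two serious points on the other side. First, the paragraph refers to a formula that is not in the text available for this review. It might contain a term that brings the answer near 17, so the route to 17 cannot be reconstructed with certainty. But the paragraph lists its inputs, and none of them is a correlation. If one was used, the published calculation is incomplete in the one input that decides the result.

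Second, the planned analysis is ANCOVA, not a t-test. A reader might infer from 33% and 41% that the trial would more likely than not miss the difference it was sized for. The document does not support that as a flat statement. If the SDs are for levels, an assumed correlation of 0.5 already brings power to about 52% with 22 per group, and 0.7 brings it to about 56% with 17. The low figures describe the unadjusted comparison only. This objection limits the claim but does not rescue the 80%, because the paragraph does not invoke ANCOVA and the correlation needed is high.

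Two further inferences should be resisted. A difference near 19.6 returns 17, and 19.6 is also the printed control SD, but nothing shows that one was mistaken for the other. Nor can it be concluded that the cited study found an unfavourable effect, since that study is not at hand. What can be said is that the label and the direction need clarifying.

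**Conclusion.** The sample size statement is wrong as written. Its stated inputs require about 55 per group, more than three times the 17 given. On those inputs an unadjusted comparison has about 33% power with 17 per group and 41% with 22, against the 80% claimed. This rests on a two-sided 5% test and on taking the printed means and SDs at face value; a one-sided test still needs 44 per group. The trial's actual power under ANCOVA cannot be determined from the document, because it depends on an unstated correlation and on whether the SDs describe levels or changes. The mislabelling of the inputs is a separate defect and does not alter the arithmetic. The paragraph must be corrected, because it is the article's only justification for the size of the trial.

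**What to change.** Keep 44 patients and rewrite the paragraph in Sample size calculation:

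1. Say whether 212.8 and 201.9 are TG levels or changes, give the units, and state which direction is benefit.
2. Remove the claim of 80% power for a difference of 10.9.
3. Replace it with the power that 17 evaluable patients per group provide: about 33% for a difference of 10.9 in an unadjusted comparison, or 80% for a difference of about 20.
4. If the size is meant to rest on the ANCOVA instead, state the assumed baseline-to-week-12 correlation and its source, and show the calculation.

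The cost is one rewritten paragraph and a less favourable power statement. No extra patients are needed and the planned analysis does not change.

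### The minimum of 17 per group cannot be reproduced from the printed sample-size inputs, which call for about 55 to 56 per group in an unadjusted two-sided comparison

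*Protocol article*

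**What the plan says.** The Sample size calculation section of the protocol article takes its inputs from a cited study and describes them as the "mean and standard deviation of TG changes in the intervention (212.8 ± 21.1") and "control (201.9 ± 19.6) groups". It sets "95% confidence, and 80% power of the test". The result is "The minimum sample size in each group was calculated to be 17 cases", raised to 22 per group to allow for dropout. No dropout rate, baseline correlation or sidedness is given. The section refers to a formula that does not appear in the text available for review.

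Elsewhere, the Participants section describes a "parallel randomized clinical trial with an allocation ratio of 1:1". Statistical methods plans an ANCOVA adjusted for baseline values and confounders, with "P < 0.05 will be considered to be statistically significant". The Abstract carries the resulting total: "44 patients with metabolic syndrome will be randomly assigned to intervention and control groups".

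**The concern.** Everything needed for a standard comparison of two means is printed: two means, two SDs, a confidence level, a power and the allocation ratio. The printed difference is only about half an SD, and 17 per group is far too few to detect that with 80% power in an unadjusted comparison.

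This is the article's only power statement, and the total of 44 rests on it. If it stays as it is, a non-significant triglyceride result could be taken as evidence against an effect from an adequately powered trial, when the data may simply be inconclusive.

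**Working it through.** **Inputs** (Sample size calculation, unless noted)

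- Means 212.8 and 201.9, so the difference is 10.9. Units are taken as mg/dl, as in the eligibility criteria.
- SDs 21.1 and 19.6. Sum of variances = 445.21 + 384.16 = 829.37. Pooled SD = √(829.37/2) = 20.36. Standardised difference = 10.9/20.36 = 0.535.
- 95% confidence, read as two-sided 0.05 (z = 1.960), and 80% power (z = 0.8416).
- Allocation 1:1 (Participants).

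**Attempt to reproduce 17**

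n per group = (1.960 + 0.8416)² × 829.37 / 10.9² = 7.849 × 829.37 / 118.81 = 54.8, so **55**. The noncentral t distribution gives 55.8, so **56**.

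Variants:

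| Calculation | n per group |
|---|---|
| One-sided, 80% power | 43.2, so 44 |
| Two-sided, one arm's SD used for both | 51 to 59 |
| Two-sided, a single variance instead of the sum | 25.4 to 29.4 |
| One-sided, a single variance | 20.0 to 23.2 |
| Power term dropped, two-sided | 26.8 |
| Power term dropped, one-sided | 18.9 |

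None gives 17. The closest, 18.9, is a one-sided calculation at 50% power and so conflicts with the stated 80%.

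**What would give 17** (normal approximation, one change at a time)

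- Difference: √(7.849 × 829.37/17) = 19.6 instead of 10.9.
- SD: 10.9 × √(17/2)/2.8016 = 11.3 instead of 20.4.
- ANCOVA on SDs of levels, with factor 1 − ρ²: 17/54.79 = 0.310, so ρ = √0.690 = 0.83.
- ANCOVA on SDs of changes: the residual variance is the change variance × (1 + ρ)/2. Even at ρ = 0 this gives 54.79 × 0.5 = 27.4, so no non-negative correlation reaches 17.

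**The step from 17 to 22.** 17/(1 − 0.20) = 21.25, rounded up to 22, so this step is consistent with 20% dropout. The rate itself is not stated.

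**Unadjusted power with the printed inputs** (two-sided t test, 2n − 2 degrees of freedom, noncentrality 0.535 × √(n/2))

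| n per group | Power | Difference detectable with 80% power |
|---|---|---|
| 17 | 32.8% | 0.991 SD = 20.2 mg/dl |
| 22 | 41.1% | 0.865 SD = 17.6 mg/dl |

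The detectable differences are 20.2/10.9 = 1.9 and 17.6/10.9 = 1.6 times the printed one. One-sided power would be 45% and 54%.

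**Power with the planned ANCOVA** (assumed baseline correlation 0.5 to 0.7; the article gives none)

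| Reading of the SDs | Residual SD, ρ = 0.5 to 0.7 | Power, n = 17 | Power, n = 22 |
|---|---|---|---|
| Levels: 20.36 × √(1 − ρ²) | 17.6 to 14.5 | 42% to 56% | 52% to 68% |
| Changes: 20.36 × √((1 + ρ)/2) | 17.6 to 18.8 | 42% to 38% | 52% to 47% |

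**The case against.** The strongest reply is that the calculation cannot be fully audited. The formula is missing from the text reviewed, and the section presents its list of inputs as not necessarily complete. A baseline correlation may have been used. On SDs of levels, about 0.83 would produce 17, and the planned analysis is a baseline-adjusted ANCOVA.

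The inputs may also be mislabelled or misprinted. Triglyceride changes above 200 are hard to credit when the eligibility threshold is 150 mg/dl. If they are levels, the intervention figure is the higher of the two. Correct arithmetic on wrongly transcribed inputs would leave the same mismatch.

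Much of this stands, and it rules out three stronger readings:

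- *That this is a proven slip in arithmetic.* The article shows only that result and inputs disagree, not which is at fault.
- *That the trial's true power is 33% to 41%, so that it is more likely to miss the effect than to find it.* Those figures belong to an unadjusted test. Under the planned ANCOVA, with SDs of levels and the assumed correlations, power at 22 per group is 52% to 68%.
- *That the plan specifies 17/22 retention.* No rate is stated, and 20% dropout leads to 22 as well.

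The mismatch itself remains. Condensing a protocol into an article can explain an omitted formula or correlation, but the article states a result that its stated inputs do not yield. Relabelling changes as levels does not alter the two-sample calculation, and the correlation that would rescue it is not stated.

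**Conclusion.** The point holds in this form: 17 per group is not reproducible from the printed inputs, and 80% power at 17 completers is not supported by them. The unadjusted requirement is 55 to 56 per group two-sided, more than three times the stated figure, so the conclusion does not turn on sidedness or on the choice between z and t.

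The size of the power shortfall is less certain. It depends on the printed means and SDs being right, on whether the SDs are of levels or changes, and on the baseline correlation. Across the assumed range of 0.5 to 0.7, no reading reaches 80%, even with all 22 per group analysed. These ANCOVA figures credit the adjustment for baseline only, not for other covariates.

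**What to change.** 1. Check the means and SDs against the cited source, and say whether they are levels or changes.
2. Print the formula, the sidedness and any baseline correlation used, then recalculate and correct the stated result.
3. If the inputs stand, keep 44 patients but withdraw 17 as the minimum for 80% power. State what 17 completers to 22 per group deliver: unadjusted power of about 33% to 41% for a difference of 10.9 mg/dl, ANCOVA power with its assumed correlation alongside, and a difference detectable with 80% power of about 18 to 20 mg/dl unadjusted.
4. State that a non-significant triglyceride result will be interpreted from the confidence interval of the adjusted difference.

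The cost is one check against the source and a rewritten sample-size paragraph. No patients are added and no procedure changes. If the inputs stand, the stated power becomes less favourable.
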